### Sample size

To evaluate the intervention, sample size was determined at the power of 80% (β = 0.2) with α set at 0.05 for an effect size of a standard deviation change of fasting serum cortisol and/or a 0.5 standard deviation reduction of body weight by the end of the intervention. This required the sample size to be a minimum of 64 participants across the control and intervention groups [37]. By considering the probable retention rate (≥95%) for a 6-month intervention the target recruitment number was fixed at a minimum of 35 participants in both the control and intervention groups, requiring recruitment of a total of 70 farming participants meeting the above criteria.

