### Impact and outcome evaluation

Impact and outcome evaluation will be achieved by assessing the immediate and longer term effects of the program. Differences in individual and group impacts and outcomes will be measured using longitudinal (3- and 6-month) data with adjustment for baseline data to evaluate any significant changes across the period of the study. The impact outcome of the anthropometric, biochemical and psychological variables of the intervention will be measured using the quasi-experimental study. Differences between intervention and control groups will be statistically ascertained.

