#### Data entry, handling and statistical analysis

Data will be tabulated and analysed using PASW^® ^statistics 18 software. Variables will be reported as means with 95% confidence intervals. Repeated measures ANOVA, paired sample t-tests, multiple linear regression, and binary logistic regression will be used to test for intervention effects after adjusting for relevant co-variables (e.g. sex, age) and baseline scores. Since physical activity scores are likely to reflect a non-normal distribution, comparisons between the sexes at baseline and over time will be performed using the Kruskal-Wallis test. Linear regression analysis will be used to assess the association between body fat percentage, body mass index and cortisol levels. Correlation coefficients between body composition, physical activity, and metabolic variables will be calculated using Pearson's and Spearman's correlation as appropriate. P values will be considered statistically significant at P < 0.05.

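### The minimum of 64 participants in total does not follow from the stated inputs for the 0.5 SD body-weight effect; 64 is the size of each group

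*Protocol article*

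**What the plan says.** The protocol article, Sample size, gives the design values: "sample size was determined at the power of 80% (β = 0.2) with α set at 0.05". Two effects are named and joined by and/or. The first is "an effect size of a standard deviation change of fasting serum cortisol and/or", which I read as 1 SD; the second is "a 0.5 standard deviation reduction of body weight by the end of the intervention". The section then concludes: "This required the sample size to be a minimum of 64 participants across the control and intervention groups".

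The next sentence allows for at least 95% retention: "the target recruitment number was fixed at a minimum of 35 participants in both the control and intervention groups", 70 in all. So 64 is meant as the sum of both groups, 32 in each.

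The question to be answered is a between-group one. Impact and outcome evaluation says: "Differences between intervention and control groups will be statistically ascertained". The same section, and the section on data entry, handling and statistical analysis, plan adjustment for baseline values. Under Study design, whole program groups are allocated to intervention or control.

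**The concern.** For a two-group comparison of means at 80% power, 64 is the familiar per-group answer for half a standard deviation. Here it appears as the total, which halves the sample. If nothing else in the plan makes up the difference, the stated power for body weight is not supported. A null result on weight could then be given more weight than it deserves, because readers would take the trial to have had an 80% chance of detecting the effect it was sized for.

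**Working it through.** **Inputs.** Power 80%, alpha 0.05, effects of 0.5 SD (body weight) and 1 SD (fasting cortisol), 64 in total, 35 recruited per group, retention at least 95%: all from Sample size. Sidedness is not stated; the analysis section says only "P values will be considered statistically significant at P < 0.05". I assume two-sided and also show one-sided.

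**Step 1: reproduce 64 for body weight.** Normal approximation, n per group = 2(1.960 + 0.842)² / d². With d = 0.5 this is 2 × 7.849 / 0.25 = 62.8, so 63. The exact two-sample t-test gives 63.8, so 64. The total is 126 to 128. The figure 64 is reproduced as a group size, not as "a minimum of 64 participants across the control and intervention groups".

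**Step 2: do other stated inputs give 64 in total?**
- 1 SD in cortisol: 16.7 per group by t-test, so 17 per group and 34 in total. No.
- One-sided alpha 0.05, 0.5 SD: 50.2 per group by t-test, so 51 per group and 102 in total. No.
- Within-group paired test, 0.5 SD: 7.849 / 0.25 = 31.4, so 32 per group by the normal approximation (33.4, so 34, by paired t-test). This comes close, but it tests change within one group, not the difference between groups.

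**Step 3: the retention step.** 64 / 0.95 = 67.4, so 68, and 70 covers it. This step is sound. In reverse, 70 × 0.95 = 66.5, or about 33 completers per group.

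**Step 4: power at the planned size (unadjusted t-test, independent participants).**

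| Completers per group | 0.5 SD, two-sided | 0.5 SD, one-sided | 1 SD, two-sided | Detectable at 80%, two-sided |
|---|---|---|---|---|
| 32 | 50.4% | 63.1% | 97.6% | 0.71 SD |
| 33 | 51.6% | 64.2% | 97.9% | 0.70 SD |
| 35 (no loss) | 54.1% | 66.5% | 98.5% | 0.68 SD |

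**Step 5: baseline adjustment.** If 0.5 SD refers to the SD of weight, ANCOVA multiplies the residual SD by √(1 − ρ²), where ρ is the baseline to 6-month correlation, so the effective d is 0.5 / √(1 − ρ²). The document gives no ρ; the values below are assumptions. Power at 33 per group, two-sided, independent participants:

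| Assumed ρ | Effective d | Power |
|---|---|---|
| 0.5 | 0.577 | 64% |
| 0.6 | 0.625 | 71% |
| 0.7 | 0.700 | 80% |
| 0.8 | 0.833 | 92% |
| 0.9 | 1.147 | over 99% |

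If 0.5 SD instead refers to the SD of the change, a comparison of changes already has d = 0.5, and power returns to about 50 to 52%.

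**Step 6: allocation by program group.** The effective sample is n / [1 + (m − 1) × ICC]. Neither the cluster size m nor the ICC is given. Assuming m from 10 to 20 and ICC from 0.01 to 0.05, the design effect runs from 1.09 to 1.95, and unadjusted power for 0.5 SD at 32 per group falls to about 48% down to 30% (normal approximation). With adjustment at ρ = 0.8, m = 20 and ICC = 0.05, power at 33 per group is about 65%.

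**The case against.** The strongest reply is that the plan does not intend an unadjusted test. Weight is measured in the same adults at baseline and 6 months, adjustment for baseline is planned in two sections, and body weight may well be highly correlated over six months. From Step 5, a correlation of 0.8 would give more than 80% power with the planned numbers if participants were independent. This stands as a possibility, and for that reason it would be wrong to say that 80% power is impossible or that the trial has an even chance of missing the effect. It does not rescue the paragraph: the Sample size section neither invokes adjustment nor gives a correlation, does not say which SD is meant, and makes no allowance for clusters.

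A reader might also infer that the trial as a whole has about 50% power. The documents do not support that: the cortisol effect, joined to the weight effect by and/or, has about 98% power at this size.

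Nor is the origin of 64 proven. The section cites a source that is not at hand, and a paired calculation or an adjusted one with a correlation near 0.71 would also lead to about 32 per group. The exact match with the per-group figure makes a mix-up the likeliest explanation, no more.

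Finally, the Background speaks of pilot testing. That softens how a null result might be read, but it does not excuse an explicit power claim.

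**Conclusion.** The point holds for body weight. The stated power, alpha and effect size do not yield the stated total: an unadjusted two-group comparison needs twice as many participants, 128 against 64. The shortfall rests on two-sided testing, no baseline adjustment and independent participants. One-sided testing narrows it but does not close it. Whether the adjusted analysis reaches 80% depends on three quantities that the section leaves open: the correlation, the SD to which 0.5 refers, and the degree of clustering. This is not detail that could be left to an analysis plan, because the article itself states the power, the effect and the number, and they do not agree.

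**What to change.** Keep recruitment at 70 and restate the Sample size paragraph in one of two ways, naming the sidedness of alpha in either case.

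1. State that about 66 completers (33 per group) give 80% power for a between-group difference of about 0.70 SD, and about 52% power for 0.5 SD in body weight, in an unadjusted comparison with independent observations. The cortisol statement can stay, with its own power given.
2. Or claim credit for baseline adjustment: state the assumed baseline to 6-month correlation with its basis, say whether 0.5 SD is the SD of weight or of change, give the ICC and cluster size, and report the resulting power.

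The cost is rewording one paragraph, with no extra participants. The downside is that the stated power for body weight may become less favourable.

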### Impact and outcome evaluation

Impact and outcome evaluation will be achieved by assessing the immediate and longer term effects of the program. Differences in individual and group impacts and outcomes will be measured using longitudinal (3- and 6-month) data with adjustment for baseline data to evaluate any significant changes across the period of the study. The impact outcome of the anthropometric, biochemical and psychological variables of the intervention will be measured using the quasi-experimental study. Differences between intervention and control groups will be statistically ascertained.

### Data collection

Trained research staff will collect the anthropometric, behavioral, dietary and activity data. They will also conduct physical, behavioral and psychological assessments.

#### 1. Physical Assessment

A complete health history will be obtained from participants registered in the Farming Fit study. Assessments will include anthropometric measures of height, weight, hip and waist circumference, body fat analysis and biochemical analysis of fasted total serum cholesterol, triglycerides, low-density cholesterol (LDL), high-density cholesterol (HDL), blood glucose and cortisol. Salivary cortisol at different time points across a 24-hour period will also be collected.

#### 2. Behavioral assessment

Alcohol habits, activity levels, dietary habits and smoking will be recorded.

#### 3. Psychosocial assessment

A validated questionnaire, the 21-question depression, anxiety, stress score (DASS 21) will be used. The DASS 21 is made up of three seven item subscales covering depression, anxiety and stress as specified in Lovibonds and Lovibond [38].

Socio-demographic, health conditions and medication data will be collected from the participant including age, gender, country of origin, health care card using the Victorian Department of Health Service Coordination Tool Templates (SCTT) [39]. The type of farming undertaken and residential postcode will also be collected from participants.

### Anthropometry

The simplicity of anthropometry allows it to be used in population-based studies to assess body-composition changes over time, as well as in clinical and field based settings where access to technology is limited. Additionally, if used in combination with biochemistry and body fat %, anthropometry can identify distinct fat distribution changes [40,41].

Participant weight will be measured (fasted) to the nearest 0.05 kg using clinically validated A&D™ precision weight scales (UC-321) taken in light clothing with shoes removed and pockets emptied. Height will be measured using a portable stadiometer (S+M™) to the nearest 0.1 cm with shoes removed and weight distributed evenly on both feet. Waist circumference will be measured to the nearest 0.1 cm at the umbilicus at the end of a normal expiration and hip circumference taken at the point yielding the maximum circumference over the buttocks using a constant tension Figure Finder Tape Measure™ [42]. Body Mass Index will be calculated as weight (kilograms) divided by height squared (in meters) to classify obesity and overweight cut-off points [43].

### Physical assessments and health condition data

Physical assessments will be conducted by a trained health professional and will include blood pressure measurement (seated BP measured after at least 5 minutes of rest taken in duplicate one minute apart), pulse rate, body fat percentage (measured by Omron™ HBF 306 Body Logic Pro Body Fat Analyser). Physical assessments will also include a general medical and behavioural assessment which will collect information on alcohol and tobacco consumption.

### Biochemical analysis

#### Lipid profile/fasting blood glucose

Total serum cholesterol, triglycerides, LDL, HDL and fasting blood glucose will be measured to assess metabolic changes associated with abdominal adiposity. Venous blood samples will be obtained following a 10-hour overnight fast. Blood samples will be transported in cold storage and analysed at a pathology biochemical laboratory.

#### Cortisol measurements

The cortisol response is consistently enhanced under chronic stress conditions and studies have demonstrated that the free cortisol response can serve as a useful index of hypothalamo-pituitary-adrenal axis (HPA) activity [26]. The secretion of cortisol, which is a marker of HPA axis activity, follows a diurnal pattern with peak levels following awakening and declining levels thereafter [44]. In this study, fasting blood cortisol will be measured in addition to salivary cortisol. Assessment of cortisol in saliva is a widely accepted and frequently employed method and is considered a valid and reliable reflection of the respective unbound hormone in blood [45]. Due to several advantages over blood cortisol analyses (e.g. stress-free sampling, less intrusive, lower costs), salivary cortisol assessment is the preferred method in basic research and clinical environments. Salivary cortisol is now an accepted, convenient method that is used to provide an indication of the variation of cortisol secretion throughout the day [45]. Salivary cortisol correlates with serum/plasma cortisol concentrations [45] and is stable at room temperature for up to 7-days [46]. Pregnancy, physical and emotional stress, strenuous activity, infection, injury and illness can increase cortisol levels. A number of drugs can also increase levels, particularly oral contraceptives (birth control pills), hydrocortisone (the synthetic form of cortisol), prednisolone and spironolactone. Therefore, the medication history of study participants will also be collected during the study.

Three groups of saliva samples will be collected using the Salivette sampling device (Sarstedt, Rommelsdorf, Germany) at baseline, three months and six months. Participants will be requested to abstain from smoking, ingesting caffeine, alcohol, food and all fluids, and strenuous physical activity for 1 h before each saliva collection. A saliva sample will be collected at approximately 09:00 hour, 12:00 hour, 16:00 hour and 20:00 hour. All saliva samples will be stored at room temperature and then spun at 3,000 × *g *for 5 min within 5 days of collection. Spun samples will be stored at -80°C until saliva cortisol levels are assayed by Radioimmunology assay (Orion Spectra Cortisol^®^).

### Survey methodology

#### Dietary assessment

Dietary intake will be measured using a one-day food record with household measures collected during a common weekday. The food record will be adapted from survey tools developed by the Dieticians Association of Australia [47]. Portion size of commonly consumed foods will be determined by using the Cancer Council of Victoria Food Frequency Questionnaire [48,49]. Daily energy, macronutrient and micronutrient intake will be determined using Foodworks Professional Edition (version 6.0.2539, Xyris Software, Brisbane, Queensland, Australia). Additionally, an 11 item food frequency questionnaire will be used to determine daily intake of fruit, vegetables, soft drinks/energy drinks, water, sweetened beverages (cordial, fruit juice, fruit drinks, and sports drinks) and weekly intake of snack foods. Frequency of daily food consumption will be categorised as follows: no consumption, 1, 2, 3, 4 and 5 serves or more. Frequency of weekly food consumption will be categorised as follows: 1, 2, 3, 4, 5, 6, 7, 8, 9 and 10 serves or more.

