## Abstract

**Background:**

Studies have confirmed that the rate of mental illness is no higher in rural Australians than that of urban Australians. However, the rate of poor mental health outcomes, and in particular suicide, is significantly raised in rural populations. This is thought to be due to lack of early diagnosis, health service access, the distance-decay effect, poor physical health determinants and access to firearms. Research conducted by the National Centre for Farmer Health between 2004 and 2009 reveals that there is a correlation between obesity and psychological distress among the farming community where suicide rates are recognised as high. Chronic stress overstimulates the regulation of the hypothalamic-pituitary-adrenal (HPA) axis that is associated with abdominal obesity. Increasing physical activity may block negative thoughts, increase social contact, positively influence brain chemistry and improve both physical and mental health. This paper describes the design of the Farming Fit study that aims to identify the effect of physical activity on psychological distress, obesity and health behaviours such as diet patterns and smoking in farm men and women.

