### Study design

This is a 6-month quasi-experimental control intervention study. Intervention and control group participants whom fulfil the abovementioned criteria will be selected from SFF programs. SFF program groups (clusters) will be randomly assigned to control and intervention groups with participants from each cluster being assigned to the same group to minimise the contamination effect.

The proposed intervention includes:

**1**. An individualised exercise coaching program for the intervention group designed by an exercise physiologist and undertaken over the entire 6-month period.

**2**. An exercise physiologist/research assistant to provide consultation on individualized exercise programs and coach over the 6-month period.

**3**. Regular monitoring of exercise activity and exercise goals by phone, email and/or mobile text message.

Participant's anthropometric and basic physical assessments and psychological assessments (DASS 21 scores) will be measured. Venous blood samples following a 10-hour fast will be taken for biochemical analysis of lipids, glucose and cortisol levels. Salivary cortisol measurements will be taken. Diet and physical activity data will be obtained using self reported questionnaires based on previously developed instruments [35,36]. Data collection will be repeated following completion of the 6-month intervention.

Diet and physical activity questionnaires and salivary cortisol samples are to be repeated following an interim 3-month period of the proposed study as outlined in Table 1. Participants from the intervention group will receive a personalised exercise program and regular phone coaching in order to promote increased physical activity.

**Table 1 T1:** Data collection and timeline for both intervention and control groups

Variable	Base line	3 month	6 month
Body weight (kg)	✓	**X**	✓
Height (cm)	✓	**X**	✓
Waist circumference (cm)	✓	**X**	✓
Hip circumference (cm)	✓	**X**	✓
Body fat (%)	✓	**X**	✓
Blood pressure (mmHg)	✓	**X**	✓
Pulse rate (bpm)	✓	**X**	✓
Fasting blood glucose (mmol/L)	✓	**X**	✓
Fasting blood cholesterol (mmol/L)	✓	**X**	✓
Fasting triglycerides (mmol/L)	✓	**X**	✓
HDL (mmol/L)	✓	**X**	✓
LDL (mmol/L)	✓	**X**	✓
Fasting blood cortisol (nmol/L)	✓	**X**	✓
Salivary cortisol*(nmol/L)	✓	✓	✓
DASS score	✓	✓	✓
Dietary questionnaire	✓	✓	✓
Physical activity questionnaire	✓	✓	✓

* Salivary cortisol will be measured by taking 4 readings/day (9 am, 12 pm, 4 pm and 8 pm)

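### As written, the weekly snack-food scale has no zero category, unlike the daily scale beside it, so non-consumers would be coded as 1 serve or left missing

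*Protocol article*

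**What the plan says.** The Dietary assessment section of the protocol article describes two instruments. The main one is a food record: "Dietary intake will be measured using a one-day food record with household measures collected during a common weekday". An 11-item food frequency questionnaire is added to it. It asks about daily intake of fruit, vegetables and several kinds of drink, and about "weekly intake of snack foods".

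Two response scales follow in consecutive sentences:

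- Daily items: "Frequency of daily food consumption will be categorised as follows: no consumption, 1, 2, 3, 4 and 5 serves or more".
- Weekly items: "Frequency of weekly food consumption will be categorised as follows: 1, 2, 3, 4, 5, 6, 7, 8, 9 and 10 serves or more".

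Snack foods are the only intake described as weekly, so the second scale applies to them.

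The Study design section provides for repeat measurement: "Diet and physical activity questionnaires and salivary cortisol samples are to be repeated following an interim 3-month period". Table 1 shows the dietary questionnaire at baseline, 3 months and 6 months. The abstract places diet within the aim, which is to identify the effect of physical activity on psychological distress and on "obesity and health behaviours such as diet patterns and smoking in farm men and women".

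**The concern.** A response scale should have a place for every possible answer. The daily scale does. The weekly scale starts at 1, and nothing else in the article supplies a code for none. This is not detail left to a fuller document: the article lists the weekly categories from first to last, directly after a list that does include a zero.

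If the scale is used as written, a participant who eats no snack food must be put into the lowest category or left without a value. Neither can be repaired later. A recorded 1 cannot be split into true ones and true zeros, and a blank cannot be told from a skipped question. The gap would recur at all three visits, so it would enter both the baseline value and the follow-up value in a baseline-adjusted comparison. What is at stake is the accuracy of one measure of diet pattern, at the end of the scale where a favourable change would finish.

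**Working it through.** The plan states no figure on this point, so there is none to reproduce. The check is whether each list of categories is exhaustive, and what follows if one is not.

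**Step 1. The two lists side by side (Dietary assessment).**

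| Scale | Categories | Code for 0? |
|---|---|---|
| Daily | 0, 1, 2, 3, 4, 5+ (6 categories) | yes |
| Weekly | 1, 2, 3, 4, 5, 6, 7, 8, 9, 10+ (10 categories) | no |

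**Step 2. Can another source supply the zero?** The food record covers one weekday. A day without snack food does not show a week without it, so the record cannot recover the missing code.

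**Step 3. If non-consumers are coded as 1.** Let the true weekly intake be k serves at one visit and 0 at a later one, with k from 1 to 9.

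- True fall: k − 0 = k.
- Recorded fall: k − 1.
- For k = 1 the recorded fall is 1 − 1 = 0, so the change is lost.
- For k = 7 the recorded fall is 7 − 1 = 6, so the change is seen but is one serve short.

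For a group with a share p of non-consumers, and setting aside the open top category:

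- Recorded mean = true mean + p × 1.
- With p between 5% and 30% (an assumption), one group's mean is overstated by 0.05 to 0.30 serves a week.
- With 35 recruited per group (Sample size section), that is 35 × 0.05 = 1.75 to 35 × 0.30 = 10.5, or about 2 to 10 people per group.

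For the comparison of intervention with control at a visit:

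- Recorded difference = true difference + (p_I − p_C) × 1.
- If p_I = p_C, the bias is zero.
- If, by assumption, p_I = 25% and p_C = 10%, the bias is 0.25 − 0.10 = 0.15 serves a week. It acts towards no effect if the intervention lowers intake.

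For change from baseline, the bias is the between-arm difference in the *change* in p. With equal shares at baseline this reduces to the same 0.15.

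**Step 4. If non-consumers are left blank.** The observed mean is then the mean among consumers, which is the true mean divided by (1 − p). Suppose consumers average m serves in both arms and the shares are again 25% and 10%:

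- True means: 0.75m (intervention) and 0.90m (control), a difference of 0.15m.
- Observed means: m and m, a difference of 0.

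Missingness here depends on the value itself, so analysing those with data does not remove the error.

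**Step 5. Which outcomes are touched?** The Sample size section rests on fasting serum cortisol and body weight. Neither uses this item, and nor does the DASS.

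**The case against.** The strongest reply is that the form is not shown. The article summarises how frequencies are categorised and does not reproduce the questionnaire, its coding manual or its skip rules. The zero in the preceding sentence is as compatible with a slip in the write-up as with a defect in the form. This stands in part. It means the first action is to look at the form, and that nobody can say from the article that non-consumers *were* miscoded. It does not remove the inconsistency, because the text sets out the weekly categories in full.

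It can also be said that the article gives no rule for non-consumers, and that the trained staff who collect the data might write in a zero or treat a blank as zero. That is possible, but it would depart from the scale as published.

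A reader might infer that a fall to zero can never be seen on this scale. The documents do not support that. Under coding as 1, only a change from 1 serve to none vanishes; larger falls remain visible, one serve short.

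A reader might also take the 0.05 to 0.30 serves as the bias in the trial's result. It is the overstatement in one group's mean, under an assumed share. An equal overstatement in both arms cancels in the comparison.

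Finally, the item is peripheral, and this stands. The intervention is exercise coaching, with no dietary component described. Diet appears in the abstract's aim but not in the aims at the end of the Background or in the Discussion. The food record is the main dietary instrument, and the statistical section names no snack-food analysis.

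**Conclusion.** The point holds as a minor one. The published weekly scale is not exhaustive, it differs from the daily scale beside it, and no other part of the article supplies the missing code.

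Under coding as 1, each non-consumer is overstated by exactly one serve, and the group comparison is biased by the between-arm difference in the share of non-consumers times 1 serve a week. The documents do not give that difference, so the 0.15 serves shown is an illustration and not an estimate. Leaving non-consumers blank gives selective missingness instead, whose size depends also on the mean intake of consumers.

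These results assume that the form matches the article and that no zero is entered off the scale. The article does not say whether snack foods are asked as one total or item by item; the arithmetic applies to whichever quantity is coded. To infer that the trial's conclusions on distress, cortisol or weight are at risk would go beyond the documents.

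**What to change.** Check the food frequency questionnaire actually in use.

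- **If it already has a zero for snack foods,** correct the sentence in the Dietary assessment section so that the text matches the form.
- **If it does not,** make no consumption the first weekly category, giving 11 categories (0 to 9, and 10 or more), consistent with the daily scale. Use the same form in both groups at baseline, 3 and 6 months.

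The article does not say whether baseline collection has begun. If it has, a mix of old and new forms would create an apparent change at the low end of the scale, so the date of the change should be recorded and earlier values of 1 and blanks flagged as ambiguous.

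The cost is one response option. Ethics approval has been granted, so a minor amendment of the form may also be needed. Sample size and the main analyses are unaffected.
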